## Abstract

**Background:**

The aging of the population has led to the increase of chronic diseases, especially dementia and cardiovascular diseases, and it has become necessary for their relatives to dedicate more time in caregiving.

The objective in the first phase of this study is to evaluate the effectiveness of a Primary Health Care procedure to increase the physical activity of people with dementia and their relative caregivers. Also the effect on the cognitive state and cardiovascular risk will be assessed.

**Methods/Design:**

Design: Clinical, multicentric and randomized trial. A simple random sampling to select 134 patients diagnosed with dementia will be carried out. After contacting their relatives, his/her participation in the trial will be requested. A basal assessment will be made and the participants will be asigned to control or intervention group (1:1). Variables: The main measure will be the assessment of physical activity (podometer and 7-PAR) in patients and caregivers. In patients with dementia: ADAS-cog, functional degree and cardiovascular risk. In caregivers: cardiovascular risk, general health and quality of life. **Intervention**: For 3 months, participants will receive instructions to do physical activity with an adapted program. This program will be designed and applied by Primary Health Care professionals in patients with dementia and their caregivers. The control group will receive regular care. **Analysis:** An intention-to-treat analysis will be carried out by comparing the observed differences between basal, 6 and 12 months measures. Change in the mean of daily steps assessed with the podometer and 7-PAR will be the main result.

**Discussion:**

If the main hypothesis is confirmed, it could be useful to improve the cognitive state of patients with dementia, as well as the cardiovascular risk of all of them. The results can be good to improve technical features of the devices that register the physical activity in the patients with dementia, and it could facilitate its commercialization.

**Trial registration:**

Clinical Trials.gov Identifier: NCT02044887.

## Background

Different types of dementia and cardiovascular diseases (CVD) are the most important health problems in elderly people. In Spain, ischemic heart disease is the main cause of losing years of life adjusted by disability in men, while the main cause in women is dementia [1]. The aging of the population has led to an increase in chronic diseases and disabilities. It has become necessary for relatives to dedicate more time in caregiving, especially women. This makes it a requirement to incorporate a gender perspective into the contents of this research about these diseases. For all these reasons it is important to find strategies to help patient with dementia (PWD) or with CVD and their relative caregivers (RC).

### Treatment of people with dementia

Nowadays it is recommended to approach the treatment of dementia with a multifactorial focus that includes both pharmacological and non-pharmacological interventions [2]. Pharmacological treatments of PWD principally address to cognitive impairment. Cognitive impairment constitutes the most relevant demonstration of dementia and it’s tend to be associated to different symptoms that affect the individual’s functional abilities, which interfere with the habitual activities and reduce their quality of life (QL) and the QL of their caregivers [3-5]. It has been found that some drugs can help delaying the development of behavioral symptoms and that these drugs can contribute in a substantial way to improve the QL of the patients, their relatives, and their caregivers. But it has also been observed that the administering of antipsychotics in PWD can increase the mortality and the risk of cerebrovascular accidents [6]. A recent review [2] concludes that the non-pharmacological therapies (NPT) can be a useful, versatile and potentially cost-effective tool to improve clinical demonstrations and the QL of the PWD, as well as the caregiver. In respect to the cognition results, functionality for the Basic Activities of Daily Living (BADL), behavior and mood, the magnitude of the effect achieved with different NPTs is similar to that observed with the use of drugs. Due to the widespread absence of secondary effects and its flexibility to be adapted to individual cases, the NPTs should be the first choice of therapy to improve the functionality of the BADL or to modify specific behaviors [2,7].

### Non-pharmacological therapies: physical activity

Several randomized clinical trials (RCTs) in PWD have shown that physical activity (PA) is a beneficial intervention for healthy older people, because it may increase the functional capacity, control for cardiovascular risk factors and slow the progression of cardiovascular disease [8,9]. It is emphasized in the reviews on the NPTs in dementia [2,10], that there is a need to carry out major RCTs in the area of physical exercise. In various RCTs with PWD, PA seems to provide benefits for the QL, problematic behaviors, depression, functionality, and falls [11,12], but they do not find evidence that it will improve CVD in the long-term. Nevertheless, recent results are encouraging [13-15] because they suggest a potentially beneficial relationship between physical activity and cognitive function, and they are designing new trials that may help clarify this issue [16-20]. Baker et al. [21] found that there was improvement in the executive control in sedentary women with CVD after six months of high intensity aerobic activity. With the current data, it seems aerobic exercise interventions are more effective than those of stretching [14,16,22]. CVD and dementia are closely related—whether in the form of Alzheimer’s disease (AD) or CVD—and they share very similar risk factors [3,23-25]. It’s possible that there are many mediation mechanisms that improve the CVDin relation to PA, by improving brain vascular function, cerebral perfusion, and the stimulation of synaptogenesis [16]. Reinforcing data from recent years suggests that modifiable behavior can have an impact on brain plasticity in human beings and animals [26]. Although unclear which mechanisms can influence the deposition of an amyloid, it is also possible that exercise can have direct relative effects on the metabolism of glucose and proteins through neurotrophic factors, neuroinflammatory factors, and cerebrovascular functioning [27]. Therefore those interventions that are recommended to improve the CVD may be beneficial to improve the cognitive level, such as walking quickly on flat terrain, at least 30 minutes every day of the week [3,23]. On the other hand, it is unclear why some cognitive functions seem to improve with physical exercise, while other functions seem to be insensitive to the change. This is an aspect that has been challenging to assess since there has been no agreement on the minimum battery of cognitive tests that must be carried out in order to detect clinically relevant and transparent changes, and that allow an increase in the reproducibility of the results in future investigations [12,19,21,25].

### Interventions with people with dementia and with their caregivers

One limitation of the effectiveness of NPT on PWD is the difficulty of carrying them out in the real environment where the PWD and caregivers are [2]. Sometimes it is only possible to do so in specialized centers and almost always is a burden for the caregiver, aggravating the negative consequences that their own care entails, such as the deterioration of the mental health, poor social support and the decrease of leisure time [28]. Of the interventions offered to CG of patients with dementia, the interventions are predominately psychosocial [2,29]. One of the recommendations that should be done is to increase the time they have for themselves, since making pleasant activities is a proven method to improving one’s mood [30]. It is therefore important to identify which activities you wish to participate in and to make a detailed list of the activities that can be increased, noting when they will take place. Pleasant activities are not only extraordinary activities like going on vacation to a far away place. They can actually be performed daily (reading the newspaper, knitting, talking with a friend on the phone, visiting friends, etc.). Additionally it is known that one of the disadvantages that the CG encounters when attempting to carry out rewarding activities is that it can be impossible to separate themselves from the patient while they are carrying out their duties [28]. On the other hand, it has been observed that it is difficult for some caregivers to make the decision to carry out pleasant activities when these activities do not directly affect the improvement of the status of the family member whom they care for [30]. A consequence of this is that the CG of PWD, when compared to non-caregivers, participate in less PA [31], show increased cardiovascular risk [32], have an increased risk of hypertension [33], and suffer more frequently from CVD [34,35]. Although these problems can be associated with the state of chronic stress related to the care, and the difficulty in expressing emotions [36], there is no doubt that they are closely related to PA restriction [30,37]. Von Kanel and col. have observed that caregivers, who reported high levels of PA, had a cardiovascular risk score similar to non-caregivers with the same level of PA [38]. These results suggest that if they increase the levels of PA, the CG could decrease their cardiovascular risk to that of the non-caregivers. It is therefore necessary to evaluate the effectiveness of carrying out interventions that encourage PA for CG of PWD [38]. In addition to assessing the degree PA of the caregivers, it seems necessary to develop interventions that specifically contribute to the increase of their PA. However, it is not easy to find interventions that have managed to increase the PA in adults, which thus would make it possible to reduce the high proportion of sedentary subjects that are in Spain. It is estimated to be 75% [8]. At the community level, a Cochrane review in 2008 concluded that there is no sufficient data to support the hypothesis that the community interventions from the multiple components effectively increase the levels of PA of the population [39]. Some RCTs developed in the field of Primary Health Care have achieved positive results, but this was only seen with the help of PA professionals or educators, and the family doctor. There was an increase of 9.7% in PA for the intervention group with the “green prescription” [40]. Other results have had discrepancies between men and women [41], and if it appears to be effective in the increasing PA of the elderly [42]. Within the framework of the European year 2012, the year of active aging and intergenerational solidarity, the HAPPIER study (Healthy Activity &Physical Programs Innovations in Elderly Residences) was initiated to be developed in elderly residences. However, there is more evidence that all patients with chronic illnesses should be refered to a rehabilitation program that includes an intervention of PA [43]. Since chronic illness is stable, it seems reasonable that it should be managed in Primary Health Care and coordinated as a regular practice. The program has been initiated into the PACE-Lift in UK in order to determine the feasibility and effectiveness of a Primary Health Care intervention with a pedometer to increase PA among older patients [44]. Our research program has participated in the project “Multi-center Evaluation of the Experimental Promotional Program of Physical Activity” (PEPAF) [8], from a sample of 5,000 subjects which were selected randomly from the population consultant in Primary Health Care of six Spanish provinces. The intervention was carried out in Primary Health Care centers and has been effective in increasing the level of PA among inactive patients [8]. Controls for PA were increased to 18 minutes per week [95% 6–31 min/week]; with an increase of the METS/hour week of 1.3 [95% Cl, 0.4 2.2]. But what is most important in relation to this new project is that the effect of the intervention was particularly positive in people older than 50 years [8], therefore it could be appropriately applied to the PWD and their CG. On the other hand, in older adults there seems to be a linear relationship between the level of activity and health outcomes, not only among the sedentary, but also among those who walk more than 12,000 steps per day [45]. Our study incorporates a particular perspective in respect to the gender differences, since more than 70% of the caregivers are women, these usually present a greater osteoarthritis, which makes them less possible to carry out PA [30].

### Evaluation of the therapeutic interventions for dementia

There are many difficulties when assessing the effectiveness of the RCTs done on the PWD, both in general and for Alzheimer’s Disease. Therefore, both the Food and Drug Administration (FDA) and the European Medicines Agency (EMEA) have developed several guides to oversee RCTs in patients with AD. It should be noted that in RCTs on Alzheimer’s Disease drugs the Evaluation Scale of Behavior-Cognitive Section (ADAS-cog) has been used almost unanimously as a measure of cognitive performance [18,46]. It is a test that provides clinically significant information, which is well considered on a conceptual and neuropsychological basis [47]. The use of the ADAS-cog as a fundamental measure of the cognitive state should be permitted to draw comparisons with the results from other NPT or even with the RCTs, taking all this into account as it has been proposed in recent trials [15,18] and that is why this measure is proposed for our intervention. Due to the multidimensional nature of PA, there is no ideal way to measure PA since it occurs in natural contexts in a set of complex leisure and instrumental behaviors. These behaviors are conducted at different levels of intensity, duration, and with different frequencies, both within one day and in different seasons of the year. Also PA involves different parts of the body that make that the measure of PA is more effective in some circumstances than in others. The majority of research for evaluating PA has been mainly in adolescents. It is necessary to carry out research that can provide information about the difficulties of measuring PA in PWD. Self-report questionnaires are the most utilized methods for evaluating PA in research. The simultaneous involvement of the accompanying family member of the PWD during the walks, as well as the completion of a validated questionnaire (7-PAR), should provide important information on the possible relationship between the characteristics of PA and PWD. A very important drawback to evaluating PA in PWD based upon the tests carried out, is related to the large variability observed in terms of the dosage (intensity and duration), modality (aerobic, muscle endurance, etc.) and scope of preparation (at the home of the patient [13,48], in residences or in hospital). In order to quantify the exercise dosage, it is important to use objective instruments to measure in this project, such as digital pedometers. On one hand it is important to know PA habits of the PWD and relatives, and on the other hand the effects of increasing their PA.

### Objectives

The objective of the first phase of this study is to evaluate the effectiveness of a Primary Health Care intervention to increase the PA of PWD and their relative caregivers and to keep the increase of PA for at least one year. The study will also evaluate if any effect is modified by age, gender, or participation as a pair. It will also be estimated the effect of the intervention on the patients in regards to their cognitive status, anthropometric measures, cardiovascular risk factors, overall health and quality of life.

### Hypothesis

There are studies that suggest that increasing PA in both PWD and CG seems to provide health benefits in both groups. However, there are no interventions that have demonstrated their effectiveness to ensure that both groups increase their PA.

Since the implementation of the project PEPAF in Primary Health Care it has been effective in increasing PA in inactive adults [8], especially among those over 50 years. We hope to demonstrate that a physical activity program that is adapted, designed, and applied by Primary Health Care professionals for patients with dementia and relative caregivers (predominantly women), is effective in increasing PA by 20% for PWD and their relative caregivers from Primary Health Care. Since the physical exercise seems to contribute and improve or slow down the cognitive impairment in PWD, we hope to reduce the ADAS-cog in PWD by 3 points. Since CVD and dementia are closely related—whether in the form of vascular cognitive impairment or in the form of Alzheimer’s Disease—and they share similar risk factors, if this program is effective, it may benefit people with dementia as well as relative caregivers, since it could help them maintain and improve their health, in particular the cognitive level of their patients and the cardiovascular problems of their CG which are derived from reduced physical activity due to the CG care tasks.

## Methods/Design

### Design

Clinical trial, multicenter studies randomized, controlled, and randomized into two parallel groups.

### Subjects

#### Study population

It will be conducted in the scope of Primary Health Care in Salamanca. There will be a simple random sampling from a list of persons who are diagnosed with dementia that belong to the participating centers. Participating physicians will confirm the inclusion criteria and the degree of evolution (GDS-FAST) Global Deterioration Scale of Reisberg. The study will contact caregivers of selected patients who meet the criteria for inclusion and they will be asked to participate in the project (Figure 1). Of those who accept, a list will be created of patients and relatives who provide care for the patient, and at least one person from this list will be selected to participate in the study. If there is more than one family member who cares for the patient at least two days a week, there will be two eligible relatives. Those who accept and meet the criteria for inclusion/exclusion must complete the informed consent document. Then they will be quoted in order to perform the initial evaluation in the Research Unit to both the PWD and the caregiver.

**Figure 1 F1:**
[figure not shown]
Study outline.

**Inclusion Criteria:** a) patient with dementia that resides in his/her home address in the area of the Primary Health Care center. b) Meets common criteria for the symptomatic diagnosis of dementia DSM-IV confirmed by the family doctor or neurologist. c) Identification of the relatives, or friends (not professional caregiver), who provides most of the care to the PWD. They do not necessarily have to live with the PWD. d) Completion of informed consent on the part of the caregiver (and PWD when appropriate).

**Exclusion Criteria** for the patients or the caregivers: a) mental disorders due to medical illnesses or related to substances (DSM-IV-TR). b) Advanced stages of dementia (GDS 6 or 7), c) Delirium. d) Comorbidity that prevents them from performing the exercise program intervention: unstable heart disease, bedridden, the need for a walker or a wheelchair, significant cerebrovascular diseases such as, bone and muscle disorders, major psychiatric, neurological or metabolic disturbances. e) Severe clinical events within the previous 6 months. f) On the waiting list of surgical interventions or treatments that require a hospital stay, or predict stays out of the capital for more than 4 weeks during the course of the intervention. g) The caregiver dissents to participate in the trial. h) Participants who submit any psychological or general medical condition that in the opinion of the investigator may impede the completion of the questionnaires in the protocol. i) Participants who are taking part at the time of the start of the study in a clinical trial or study involving medications. The PWD take medications that may negatively affect cognitive function: anticholinergics (i.e. amitriptyline), major tranquilizers (antipsychotic typical and atypical) and anticonvulsants. g) Changes in the medication for PWD that they can take for cognitive function (memantine, rivastigmine, donepezil, galantamine) during the period of intervention.

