### Baseline evaluation and follow-up

The initial information will be collected in the 1^st^ visit: It’s comprised of 3 groups of assessments (carried out by different professionals): A) The initial (health) screening: diagnostic criteria, GDS, dementia (Blessed, Timlison and Roth, 1968), informed consent, characteristics of care (duration, intensity, social support), informant questionnaire (TIN), socio-demographic data, comorbidity. B) Psychology: a) Patient: Mini Mental State Examination, ADAS-cog, 7-Minute Screen Test. C) Nursing: Cardiovascular evaluation, anthropometric measures, pedometers. b) The caregiver: Quality of Life (SF-12), Overload and burden (Zarit Breve), Mental Health (GHQ-12), Family Functioning (APGAR-F). In VISIT 2, after 7 days, the pedometers and activity log will be collected (7-PAR); It will be confirmed to the Principal Investigator that the initial information is complete and the pair will be assigned to the corresponding group (intervention or control (1:1) according to the previously maid random sequence. At 6 and 12 months the baseline evaluation will be repeated for both the CG and PWD. The flow chart (Figure 1) details the phases and steps in the development of the clinical trial.

Information on the activities carried out, difficulties in performing them, activity log, etc. will be collected during the interviews when the pedometer is collected. After the 6 month evaluation, there will be at least one meeting with the caregivers in the intervention group and another with the control group to complete the information about the development of the program and the proposals that have been considered more efficient to better record the PA (use of pedometers, etc.) and, in the intervention group, contributions are also prompted to increase the PA in their environment.

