### Intervention

During the 3 months they will receive instructions to perform PA autonomously (walking, preferably in the vicinity of the place of residence). The intervention will be conducted by a professional from the health center so only pairs from the intervention group will have knowledge of the specific recommendations of the AFISDEMYF. There will be a 15-minute interview each month. This is an intervention that has demonstrated its effectiveness in the PEPAF study [8] and adapted, designed, and been implemented by Primary Health Care professionals for dementia patients and their relative caregivers.

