### Statistical analysis

The analysis will take place using the intent- to-treat (ITT) The observed improvements will be compared between the basal measurement, at 6 and 12 months for each subject assigned to the intervention groups with respect to those assigned to the control group. The size of the effect will be defined as the change post-treatment in the experimental group less the change post-treatment in the control group, divided by the standard deviation combined. The effect of the intervention will be attributable to the differences in such improvements in these groups. A 95% confidence interval will be calculated. Predictor variables will be analyzed and confounding factors: sex, age, and it will be estimated the time’s effect on the repeated measurements that were carried out, using mixed linear regression models, fixed effects (time, intervention, interaction between time and intervention) and at random. The data was analyzed using IBM® SPSS® v.20 software.

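### The exclusion for cognitive-drug changes during the intervention can be met only after randomisation; applied as written, it would conflict with intention to treat

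*Protocol article*

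**What the plan says.** All references are to the protocol article.

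- **Exclusion criteria (Subjects).** The last item in the list is "Changes in the medication for PWD that they can take for cognitive function (memantine, rivastigmine, donepezil, galantamine) during the period of intervention". An earlier item in the same list also concerns the intervention period but is worded as a forecast: "predict stays out of the capital for more than 4 weeks during the course of the intervention".
- **Study population.** Eligibility is settled at entry: "Those who accept and meet the criteria for inclusion/exclusion must complete the informed consent document".
- **Baseline evaluation and follow-up.** At visit 2, after the seven-day pedometer week and once baseline data are complete, "the pair will be assigned to the corresponding group (intervention or control (1:1) according to the previously maid random sequence". The baseline evaluation is repeated at 6 and 12 months for patient and caregiver.
- **Intervention.** "During the 3 months they will receive instructions to perform PA autonomously", with a short monthly interview.
- **Timeline.** Every pair is to be evaluated again at 6 and 12 months.
- **Statistical analysis.** The analysis is by intention to treat, and improvements are compared "for each subject assigned to the intervention groups with respect to those assigned to the control group".
- **Methodological limitations.** Participants are not blinded.
- **Variables and measurement instruments.** Medication linked to cognitive impairment is logged.

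**The concern.** An eligibility rule has to be decidable before randomisation. This one refers to something that happens, or does not happen, in the three months after assignment. A site that follows the wording can act on it only by excluding a patient who has already been randomised.

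The groups compared would then no longer be the randomised groups. A change in a cognitive drug may well follow perceived decline, so the excluded patients could be selected on the course of their cognition. Because participants know their arm, the frequency of such changes could also differ between arms. ADAS-cog, the primary cognitive measure, is the outcome most exposed. Any exclusion would also reduce the number analysed for the main result, the step count, in a trial whose sample size allows for 5% loss. A larger sample would restore power but would not cure selection after randomisation.

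**Working it through.** **1. Order of events**

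| Step | Section | Timing relative to randomisation |
|---|---|---|
| Criteria checked, consent | Study population | before |
| Baseline, 7-day pedometer week | Baseline evaluation and follow-up | before |
| Pair assigned 1:1 at visit 2 | Baseline evaluation and follow-up | randomisation |
| Three-month intervention | Intervention | after |
| Event named in the drug criterion | Exclusion criteria | after |
| Evaluations at 6 and 12 months, every pair | Baseline evaluation and follow-up; Timeline | after |
| Comparison as assigned | Statistical analysis | after |

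The criterion is checked in the first row but can be met only in the fifth. Acting on it there would contradict the last two rows.

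**2. The plan's own sample size**

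Inputs from Sample size: difference 600 steps/day, SD 1200, two-sided alpha 0.05, power 80%, 5% loss.

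n per group = 2 × [1200 × (1.96 + 0.84) / 600]² = 62.8, rounded up to 63. Then 63 / 0.95 = 66.3, rounded up to 67, or 134 in total. The stated figure reproduces, so the point changes no number in the plan. After 5% loss, 67 × 0.95 = 63.65 per group remain, which leaves almost no room for further removals.

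**3. Power for steps if the criterion removed equal shares of both arms**

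The removed shares are assumptions, because the documents give no rate of drug change. Power is for a two-sample t-test at a standardised difference of 600 / 1200 = 0.5, with 63.65 × (1 − share) per arm.

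| Share removed | n per arm | Power (t) | Power (normal approximation) |
|---|---|---|---|
| 0% | 63.65 | 79.9% | 80.5% |
| 10% | 57.3 | 75.6% | 76.3% |
| 15% | 54.1 | 73.1% | 73.9% |
| 20% | 50.9 | 70.5% | 71.3% |

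**4. Bias in ADAS-cog if the shares differed by arm**

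Assumptions, none of them from the documents: no true effect; SD of ADAS-cog change 6; correlation 0.5 between decline and the tendency to a drug change; the patients with the highest tendency are removed.

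With a share p removed, the mean change among those who remain shifts by 0.5 × 6 × h(p), where h(p) = φ(z) / (1 − p) and z cuts off the upper share p of a standard normal distribution. This gives h(0.05) = 0.109, h(0.10) = 0.195, h(0.20) = 0.350 and h(0.25) = 0.424. The spurious difference between arms is 3 × [h(p₁) − h(p₂)]:

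- 10% vs 5%: 3 × (0.195 − 0.109) = 0.26 points
- 20% vs 10%: 3 × (0.350 − 0.195) = 0.46 points
- 25% vs 10%: 3 × (0.424 − 0.195) = 0.69 points

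The Hypothesis section hopes for 3 points. At a correlation of 0.2 the first case falls to 1.2 × 0.086 = 0.10 points. If more controls are removed, the shift favours control and could hide a benefit; if more intervention patients are removed, it exaggerates one. With equal removal the average bias is zero under these assumptions.

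**The case against.** The strongest reply is that the protocol never says a randomised pair is withdrawn, left unmeasured or left out of the analysis. Criteria are applied at one stated step, before consent. Visit 2 checks only that baseline information is complete. The follow-up and timeline text have every pair evaluated again, and the analysis compares subjects as assigned. All of this points to retention. That objection stands. A reader might infer that the trial removes patients after randomisation, but the documents do not support that stronger statement.

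A second reply is that the item means changes expected at screening, which would conflict with nothing. That reading is possible, and the English of the article is uneven enough that one missing word is not strong evidence. Still, it is not what the text says: where the same list means a forecast, it says so. If the milder meaning was intended, the sentence still needs rewording so that the participating centres apply it alike.

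Three further inferences about harm also go beyond the documents. Nothing says that the caregiver's data are lost when the patient's drug changes. Nothing says that the prescriber knows the arm; what is stated is that participants are unblinded and assessors are not told the allocation. And the sample-size text does not spell out what the 5% loss covers, so it cannot be said that removals would necessarily come on top of it.

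Finally, the figures rest wholly on assumed rates, one assumed SD and assumed correlations. They show no bias for steps, the main result. ADAS-cog is secondary, and the limitations section already accepts that clinically relevant conclusions on it would need longer follow-up. These objections limit the severity. They do not remove the conflict in the wording.

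**Conclusion.** The concern holds in a limited form. A stated exclusion criterion depends on an event that can be observed only after assignment. Followed literally, it would exclude randomised patients, against the intention-to-treat comparison and the promise to re-evaluate every pair. Whether anyone would be excluded is not stated, so the passages are in conflict but no removal has been shown.

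The size is unknown. On the assumed values (SD 6, correlation 0.5, removal from 10% vs 5% up to 25% vs 10%), the bias in ADAS-cog would be about 0.3 to 0.7 points against a hoped-for 3, and smaller with a weaker correlation. With 10% to 20% removed equally, power for 600 steps/day would be about 76% to 70% instead of 80%. The planned 134 is not in error. This is a should-fix: the harm depends on how the rule is applied, while the cure is cheap.

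**What to change.** Reconcile Study population, the exclusion criteria, Baseline evaluation and follow-up, Timeline and Statistical analysis in two sentences:

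1. Limit the drug-change criterion to what can be judged before randomisation.
2. State that every randomised pair stays in follow-up and in the intention-to-treat analysis whatever drug changes occur, and that changes are recorded as post-randomisation events. Medication is already logged, so little new data collection is needed.

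How the drugs themselves are managed is a clinical matter and is not addressed here. A sensitivity analysis of ADAS-cog that takes drug changes into account is optional and can be left to the SAP.

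The cost is a short amendment. The article reports that the trial is still recruiting, so the wording can be settled while pairs are still being enrolled. The downside is that some noise from drug changes stays in the ADAS-cog comparison.
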